## Abstract

There is growing interest in the investigation of ketogenic diets as a potential therapy for bipolar disorder. The overlapping pharmacotherapies utilized for both bipolar disorder and seizures suggest that a mechanistic overlap may exist between these conditions, with fasting and the ketogenic diet representing the most time-proven therapies for seizure control. Recently, preliminary evidence has begun to emerge supporting a potential role for ketogenic diets in treating bipolar disorder. Notably, some patients may struggle to initiate a strict diet in the midst of a mood episode or significant life stressors. The key question addressed by this pilot clinical trial protocol is if benefits can be achieved with a less restrictive diet, as this would allow such an intervention to be accessible for more patients. Recent development of so-called ketone esters, that once ingested is converted to natural ketone bodies, combined with low glycemic index dietary changes has the potential to mimic two foundational components of therapeutic ketosis: high levels of ketones and minimal spiking of glucose/insulin. This pilot clinical trial protocol thus aims to investigate the effect of a ‘ketogenic-mimicking diet’ (combining supplementation of ketone esters with a low glycemic index dietary intervention) on neural network stability, mood, and biomarker outcomes in the setting of bipolar disorder. Positive findings obtained via this pilot clinical trial protocol may support future target engagement studies of ketogenic-mimicking diets or related ketogenic interventions. A lack of positive findings, in contrast, may justify a focus on more strict dietary interventions for future research.

## 1. Introduction

Bipolar disorder is a disabling chronic condition that poses unique challenges to treatment [1,2,3,4]. Treatment of bipolar depression is less well investigated than treatment of unipolar depression, with antidepressant treatment bearing additional risks of evoking mania, destabilizing mood, and inducing dysphoria or potential suicidality in the context of bipolar disorder [5,6,7,8]. On the other side of the spectrum, it is not uncommon for patients to exemplify inconsistent (or nonexistent) adherence to a mood stabilizer regimen for the treatment of mood elevation. Among patients with bipolar disorder, doubts about the need for medications as well as concerns for adverse effects have been cited as drivers of markedly high rates of medication nonadherence, which may approach 50% (or potentially as high as 69% by some estimates) [9,10].

With a patient-centered approach to care, global functioning represents another important consideration alongside symptomatic relief. In a study that followed patients for 2–4 years after their first hospitalization for mania, 28% of patients remained symptomatic and 57% did not return to their prior level of functioning [11]. While pharmacological breakthroughs have provided undeniable value and saved countless lives, these findings suggest the possibility that existing therapeutic paradigms may be further improved upon as our understanding of this disorder evolves.

What remains unknown is how exactly clinical practice can be further advanced, particularly in light of an evolving pathophysiological understanding of bipolar disorder. While emerging evidence supports a potential role for metabolic interventions such as a ketogenic diet in the treatment of this complex disorder, this possibility raises further questions related to policy challenges and insurance reimbursement hurdles affecting the delivery of care for nutrition-related interventions. Whereas nutrition-related interventions offer the possibility of transformative pleiotropic benefits, they are also considered to be more complex to incorporate into research methodology and clinical practice as compared to pharmaceutical treatments. Adherence represents a key consideration in psychiatric populations, providing an impetus to consider interventions that may be more easily implemented for patients who struggle with self-discipline or are in the midst of significant life stressors. Drawing on this line of reasoning, investigation of exogenous ketone supplements may reveal strategies for improving the accessibility of therapeutic ketosis. To the authors’ best knowledge, there is not a single clinical study investigating exogenous ketone supplementation in the setting of bipolar disorder to date.

Importantly, the effects of exogenous ketone supplementation are widely known to be modulated by dietary intake (in particular, glycemic/insulin spiking). Exogenous ketone supplementation without any other dietary changes may thus confer limited benefit depending on the clinical context. As a potential middle ground, combining exogenous ketone supplementation with low glycemic index dietary changes may mimic two foundational components of strict ketogenic diets: namely, high levels of ketones and minimal glycemic/insulin spiking. This pilot clinical trial protocol thus aims to investigate the biomechanistic effects of exogenous ketone supplementation combined with low glycemic index dietary changes in the setting of bipolar disorder.

## 2. Biomechanistic Rationale

Although the exact mechanisms underlying bipolar disorder remain unclear, it is evident that agents implicated in neuronal membrane stability are effective in mitigating symptoms [12,13,14,15,16]. The overlapping pharmacotherapies utilized for both bipolar disorder and seizures suggest that a mechanistic overlap may exist between these conditions. A corollary hypothesis derived from this possibility is that treatments with proven efficacy in the realm of seizure management may also prove to be beneficial for patients with bipolar disorder. Interestingly, one of the most time-proven approaches to seizure control is the induction of ketosis, with Hippocrates himself documenting fasting as a remedy for seizures [17]. In 1921, [name] at the Mayo Clinic postulated that the benefits of fasting may be dependent on high levels of ketones in the blood, speculating that similar benefits may be derived if ketonemia was achieved by other means [18]. Hence, the ketogenic diet was born, with breakthroughs that followed in the treatment of seizures.

With these considerations in mind, the ketogenic diet may also offer a promising novel therapeutic option for patients suffering from bipolar disorder. This hypothesis has been supported by limited preliminary data. In a study by Phelps et al. [19] two women with bipolar disorder were able to maintain the ketogenic diet for at least two years. Both women tolerated the diet well and achieved mood stabilization exceeding that attained with medication, reporting subjective improvement distinctly related to ketosis. Ultimately, both patients were able to discontinue mood-stabilizing medications and maintain mood stability with the ketogenic diet as a stand-alone intervention. In a data mining analysis comparing hundreds of anecdotal reports from online bipolar disorder forums, Campbell et al. [20] found that reports of symptomatic remission were significantly higher for the ketogenic diet in comparison to other health-conscious diets (with approximately 73% of reports endorsing some degree of mood stabilization with the ketogenic diet, as compared to approximately 54% of reports endorsing some degree of mood stabilization with other health-conscious diets). More recently, a retrospective analysis that included 13 patients with bipolar disorder reported significant clinical improvements when the ketogenic diet was utilized in an inpatient setting (depressive symptom severity was reduced by over 60%, with concordant improvements in clinical global impression) [21].

Conceptually, there are other reasons to investigate ketogenic interventions as a potential treatment modality for patients with bipolar disorder. Accumulating evidence has provided increasing support for the hypothesis that mitochondrial dysfunction may be an underlying feature of bipolar disorder [22,23,24]. Notably, mitochondrial dysfunction has also been implicated in the pathogenesis of epilepsy [25]. Considering the profound mitochondrial effects of ketogenic interventions, it is plausible that improved bioenergetic efficiency attained via therapeutic ketosis may promote stabilization of cellular functioning and, thereby, clinical improvement. Notably, the Na^+^/K^+^ ATPase, responsible for regulating neuronal membrane potential, represents a major beneficiary of bioenergetic availability. By some estimates, this ATPase consumes nearly half of the ATP in the brain [26]. In a setting of Na^+^/K^+^ ATPase hypofunctionality, sodium would be expected to accumulate within neurons, altering resting potential (and, thereby, altering patterns of neuronal excitability). Interestingly, individuals with bipolar disorder have been observed to exhibit decreased Na^+^/K^+^ ATPase activity and increased intracellular sodium concentrations [27]. Moreover, mood stabilizers shown to be effective in bipolar disorder converge upon a shared mechanism: reduction of intracellular sodium concentrations [14,28,29,30]. Similarly, ketogenic interventions may also converge upon this mechanism. In addition to powering the Na^+^/K^+^ ATPase by supporting mitochondrial energetic output, therapeutic ketosis may also lower intracellular sodium by inducing a mildly acidotic state, as extracellular protons will be exchanged for intracellular sodium [31,32,33]. An acidic neuronal environment also reduces neuronal excitability via a variety of other mechanisms, including modulation of calcium channel conductance [34]. Furthermore, a ketogenic diet may elevate GABA/glutamate ratios, an effect mediated by the gut-brain axis [35,36,37]. Modulation of neuronal excitability is thus a plausible mechanism attributable to ketogenic interventions, particularly in light of the clinical outcomes achieved by the ketogenic diet in the realm of epilepsy.

Altered patterns of synaptic plasticity have also been identified in the setting of bipolar disorder, bearing implications for interventions that modulate synaptic plasticity [38]. Animal models have demonstrated that ketone bodies are capable of stimulating brain-derived neurotrophic factor (BDNF) production [39,40], converging with evidence in human research [41,42,43]. BDNF is widely known as a vital modulator of synaptic plasticity.

Looking beyond the level of the synapse, a growing body of functional neuroimaging research has revealed that bipolar disorder is characterized by abnormalities in neural network functional connectivity. In particular, altered interactions between the amygdala and prefrontal regions have been implicated in bipolar disorder [44]. Via an elegant fMRI analysis, Mujica-Parody et al. [45] found that the ketogenic diet has a stabilizing effect on neural network functional connectivity. Moreover, exogenous ketone esters also demonstrated a stabilizing effect on neural network functional connectivity, even if consumed in the setting of a regular diet. Theoretically, the stabilization of neural networks may also bear implications for the management of bipolar disorder. This line of reasoning would be consistent with patterns of altered neuronal excitability identified in the setting of bipolar disorder [46], as altered patterns of spreading activation would be an expected downstream effect of altered neuronal excitability.

Furthermore, with a growing body of evidence demonstrating intersections between neuroinflammatory processes and psychiatric disorders, it is plausible that the anti-inflammatory properties of ketone bodies may prove to be therapeutic for patients suffering from bipolar disorder [47,48,49]. Neuroinflammatory processes have been implicated in the pathogenesis of the bipolar disorder, as demonstrated via markers of excitotoxicity and neuroinflammation mediated by the IL-R cascade [50]. Ketone bodies have been shown to inhibit activation of the NF-κB inflammasome (a key orchestrator of this signaling cascade) [51,52].

Intertwined with all of these factors, a final consideration is the role of epigenetics in the pathophysiology of bipolar disorder. In light of the clear impact of environmental factors on this episodic disorder, it is plausible that fluctuations in epigenetic expression may underlie shifts in symptomatology. Of particular relevance to this trial is the finding that ketone metabolism drives activation of sirtuins (which have been referred to as “the guardians of the genome” given their central role in epigenetic regulation), in addition to modulating epigenetic expression via a variety of other mechanisms [53,54,55,56].

## 3. Methods

### 3.1. Study Design: Overview

At the time of this writing, many scientific questions remain unanswered with a clear need for further research. In designing a pilot study, it is important to consider the distinction between a strict ketogenic diet and exogenous ketones, the latter of which can be consumed in a supplementary manner while maintaining a regular or modified diet. Clinical benefits derived from the ketogenic diet are likely attributable to a combination of low glycemic index and the direct (and indirect) metabolic/signaling effects of ketone bodies themselves. However, the proportional contribution from each of these components is not fully understood and likely varies based on the clinical setting. While a strict ketogenic diet encapsulates the entirety of these potential contributory components, it also sets a high bar for adherence in a population that already struggles with treatment adherence. In order to optimize ease of adherence, we propose supplementation of exogenous ketone esters combined with a low glycemic index diet for this pilot study, which will track clinical outcomes and global functioning metrics alongside metabolic markers. Moreover, given the stabilizing effects on neural networks demonstrated with exogenous ketone ester supplementation, the protocol features collection of baseline and follow-up fMRI data to assess neural network stability before and after the intervention. Combining clinical assessments, metabolic markers, and functional neuroimaging data into a multifaceted analysis will provide a comprehensive window into the dysregulation underlying bipolar disorder and the mechanisms by which this metabolic intervention may affect outcomes for our patients.

### 3.2. Experimental Intervention

The overarching goal of this open-label, exploratory pilot study is to explore biomechanistic effects of exogenous ketone supplementation combined with a low glycemic diet (in effect, a ‘ketogenic-mimicking diet’) for patients with bipolar disorder. This represents a less restrictive metabolic intervention compared to a strict ketogenic diet while replicating two foundational elements of therapeutic ketosis: low levels of glycemic/insulin signaling and high levels of circulating ketones. In addition to assessments of mood stability and global functioning, we will obtain functional neuroimaging data to better characterize the biomechanistic effects of this intervention.

### 3.3. Outcome Measures

Primary outcome measure:Neural network stability as ascertained via functional magnetic resonance imaging (fMRI)

Secondary outcome measures:Neural uptake of ketone bodies as ascertained via magnetic resonance spectroscopy (MRS)Clinical assessments and global functioning metrics (see Table 1)Laboratory assessments (see Table 2)Continuous glucose monitoring (CGM) glycemic trendsß-hydroxybutyrate (ß-HB) blood level (as ascertained via Keto-Mojo™ monitoring device)Sleep quality (as ascertained via Oura™ biometric ring)

Primary Aim: To compare fMRI neural network stability before and after a low glycemic index dietary intervention combined with open-label supplementation of exogenous ketones, namely bis hexanoyl (R)-1,3-butanediol (available over the counter as an athletic performance and health supplement called Juvenescence ‘Metabolic Switch^®^’ powder and also referred to as ‘C6 ketone di-ester’) in a biomechanistic pilot study in individuals with bipolar disorder (*n* = 34 [please see Supplementary Materials for sample size calculation]). While a comprehensive low glycemic index diet may also be considered to augment the effects of exogenous ketone supplementation, for simplicity and ease of adherence the low glycemic index intervention in this protocol will be comprised of four simple dietary changes as follows:Not consuming soda for the duration of the intervention period.Not consuming candy/sweets for the duration of the intervention period.Not consuming white grains/rice for the duration of the intervention period, instead replacing these with complex carbohydrates such as whole grains and brown rice.If consuming fruit with a meal, eating the fruit at the end of the meal to minimize glycemic spiking.

Timetable: This study, to be completed over a 3-year period, will include a net total of *n* = 34 subjects with bipolar disorder. Details of the enrollment and major test procedures are outlined in Table 3. Milestone of recruitment success is net completion of 24 persons by the end of year 2. A gross total of up to 50 subjects will be recruited to account for possible attrition.

Design: Exploratory pilot study assessing open-label ketone ester supplementation (19 g BID PO; 12.5 g active ingredient per serving) in combination with low glycemic index dietary intervention.

Inclusion criteria

To be eligible for the study, an individual must meet the following criteria:Adults 18 and older, able to provide informed consentDiagnosis of bipolar disorder (any subtype)

Exclusion criteria

An individual who meets any of the following criteria will be excluded from participation in the study:History of traumatic brain injuryEvidence of large vessel stroke or mass lesion on MRIHistory of significant gastrointestinal disease or malabsorptive disorderPregnancy or breastfeedingUncontrolled diabetes mellitusHistory of mitochondrial disorder and/or significant uncontrolled metabolic/medical disorderActive/current substance dependence (and/or consumption of two or more alcoholic beverages per day)Subjects with contra-indications to MR imaging, including pacemakers or severe claustrophobiaActive suicidal or homicidal ideation

Study procedures and assessments: After obtaining informed consent and screening for study eligibility, study participants will undergo the baseline clinical assessment and imaging protocol (separate days). There will be a total of 5 visits for this pilot study. The baseline clinical assessment will include standardized assessments of global functioning and symptom severity (summarized in Table 1). Participants will also be instructed to wear a continuous glucose monitor (CGM) and a biometric device called Oura™ ring for 7 (±3) days prior to starting the intervention, allowing for assessment of baseline glycemic trends as well as sleep and activity data. They will also have their blood drawn for laboratory assessments at the pre-intervention clinical visit (assays detailed in Table 2)—blood-derived laboratory assays will be optional for participants (e.g., to accommodate participants with a strong preference to avoid blood draws or a specific phobia pertaining to blood). Upon completion of this baseline assessment, participants will initiate the 90 (±10)-day intervention (ketone ester supplementation in combination with low glycemic index dietary changes). During the intervention period, participants will be prompted to submit daily ratings of mood via the CareEvolution platform. They will also be instructed to check their blood ketone/glucose levels using a Keto-Mojo™ ketone/glucose monitor on intervention days 0 (baseline), 45 (±10) (mid-intervention), and 90 (±10) (post-intervention): measurements will be taken before supplementation (morning fasting) and two hours post-supplementation. At the mid-intervention point (day 45 ± 10 days), participants will repeat the comprehensive neurobehavioral assessment summarized in Table 1. At the end of the intervention period, they will repeat a 7–10 day CGM assessment. After completing the intervention, participants will repeat the clinical/laboratory assessments and imaging protocol (on separate days). They will continue to wear their Oura™ ring throughout the intervention period and for a 14 (±7)-day post-intervention follow-up period. Daily mood ratings will also be continued during this post-intervention follow-up period until the Oura™ wearable is returned, at which point study participation will be completed. For a visual overview of this study design, please refer to the schedule of events outlined in Table 3 and the flowchart depicted in Figure 1. A visual overview of key outcome metrics is featured in Figure 2.

**Table 3 nutrients-15-03068-t003:** Study Overview.

Outcome Metric	Pre-Intervention Imaging *	Baseline Clinical Assessment *	Daily	Mid-Intervention	Post-Intervention Imaging *	Post-Intervention Clinical Assessment *
fMRI/MRS	X				X	
CGM	X	X			X	X
Oura™	X	X	X	X	X	X
YMRS		X		X		X
BDI		X		X		X
PHQ-9		X		X		X
Mood Surveys		X	X	X		X
CGI		X		X		X
GAF		X		X		X
LFQ		X		X		X
SDS		X		X		X
STAI		X		X		X
SF-36		X		X		X
Blood ketones		X		X		X
Blood glucose		X		X		X
Lab assays (see Table 2)		X				X

* For visits 1–2 and 4–5: There is no pre-set sequence for which assessment (clinical or imaging) comes first.

**Hypothesis 1**.
*Neural network stability in subjects with bipolar disorder will improve after the approximately 90-day intervention involving supplementation with 19 g BID PO of ketone ester (containing 12.5 g C6 ketone di-ester per serving).*

**Hypothesis 2**.
*Greater neural uptake of ketone bodies as measured via MRS will correlate with greater improvement in neural network stability.*

**Hypothesis 3**.
*Greater glucose lability (glucose spikes demonstrated via CGM trends) will correlate with less favorable response to the intervention.*

**Hypothesis 4**.
*Lower Glucose Ketone Index (GKI) (as measured via Keto-Mojo™ device) will correlate with more favorable response to the intervention.*

Exploratory Hypothesis 1: Neural network instability as ascertained via fMRI may correlate with mood instability as ascertained via self-reported mood surveys.

Exploratory Hypothesis 2: Ketone ester supplementation combined with low glycemic index dietary changes may correlate with improved metabolic biomarkers (e.g., hs-CRP or serum lactate).

Exploratory Hypothesis 3: Greater neural uptake of ketone bodies as measured via MRS and greater increases in blood ketone level as measured via Keto-Mojo™ device may correlate with greater improvements in mood stability and global functioning.

Impact: Positive findings in this small exploratory pilot study may support future target engagement studies of ketone ester supplementation or other ketogenic interventions in bipolar disorder.

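### No blood ketone reading is scheduled at the MRS scans, so 'neural uptake' cannot be told apart from the circulating ketone level at the scan

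*Protocol article*

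**What the plan says.** Section 3.3 of the protocol article names as a secondary outcome "Neural uptake of ketone bodies as ascertained via magnetic resonance spectroscopy (MRS". Hypothesis 2 uses it as the explanatory variable: "Greater neural uptake of ketone bodies as measured via MRS will correlate with greater improvement in neural network stability". Exploratory Hypothesis 3 lists MRS uptake and the rise in blood ketone level as two different quantities.

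The timing is set in three places:

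- **Table 3.** The fMRI/MRS row is marked only under pre- and post-intervention imaging. The row "Blood ketones" is marked under baseline clinical, mid-intervention and post-intervention clinical, and under neither imaging column.
- **Section 3.3, study procedures.** Participants use a "ketone/glucose monitor on intervention days 0 (baseline), 45 (±10) (mid-intervention), and 90 (±10) (post-intervention"; the "measurements will be taken before supplementation (morning fasting) and two hours post-supplementation". On the end-of-study visits: "After completing the intervention, participants will repeat the clinical/laboratory assessments and imaging protocol (on separate days".
- **Table 3 footnote.** On the order of visits 1–2 and 4–5: "There is no pre-set sequence for which assessment (clinical or imaging) comes first".

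Section 4 assigns mixed linear modelling to the change in network stability and in MRS uptake, and says no more about MRS.

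**The concern.** An MRS acquisition shows the ketone present in brain tissue at that moment. The amount depends on how much the blood is delivering and on how readily the brain takes it up. To attribute a difference between participants to uptake, one needs the blood level at the time of the scan. The published schedule provides none. The readings it does provide fall at other visits, at an interval from the scan that varies because the visit order is free.

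What is at stake is the reading of Hypothesis 2 and of the MRS part of Exploratory Hypothesis 3. Table 3 lists fMRI and MRS as one item. If both come from one session, a high blood ketone level that day could raise the MRS signal and also shift network stability. The article supplies that route itself, since Sections 2 and 3.1 cite a stabilising effect of ketone esters on networks. A positive correlation could then arise without any difference in uptake. Conversely, variation in blood level could hide a real relation with uptake and produce a null.

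**Working it through.** **Step 1: the schedule.** The plan has no figure of its own on this point to reproduce. The sample size of 34 belongs to the primary aim and is not in question here. Setting the sources side by side:

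| | Imaging visits | Clinical assessments | Mid-intervention |
|---|---|---|---|
| fMRI/MRS | yes | no | no |
| Blood ketones | no | yes | yes |
| CGM | yes | yes | no |
| Oura ring | yes | yes | yes |

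Table 3 does mark measures in the imaging columns where they are intended (CGM, Oura). Blood ketones are placed elsewhere, and clinical and imaging assessments are on separate days. CGM may cover glucose at the scan; nothing scheduled covers ß-HB.

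**Step 2: what the signal contains.** Take one MRS value per participant and write

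log(MRS) = log(blood level at scan) + log(uptake fraction),

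with the two terms independent. This model is an assumption, as are all coefficients of variation (CVs) below; the documents give no variances. For a lognormal quantity the log variance is ln(1 + CV²):

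- CV 0.2: ln(1.04) = 0.0392
- CV 0.3: ln(1.09) = 0.0862
- CV 0.4: ln(1.16) = 0.1484
- CV 0.5: ln(1.25) = 0.2231

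Blood share of log-MRS variance = blood variance / (blood variance + uptake variance):

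- blood 0.2, uptake 0.4: 0.0392/0.1876 = 21%
- blood 0.3, uptake 0.3: 0.0862/0.1724 = 50%
- blood 0.4, uptake 0.2: 0.1484/0.1876 = 79%
- blood 0.5, uptake 0.2: 0.2231/0.2623 = 85%

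**Step 3: effect on Hypothesis 2.** Suppose stability has a true correlation of 0.6 (assumed) with one component only. The expected MRS–stability correlation is 0.6 × √(blood share) if that component is blood level, and 0.6 × √(1 − blood share) if it is uptake. A simulation with n = 34 and 20,000 replicates gave the same averages to two decimals. It also gave the share of trials with a significant positive correlation (two-sided 5% test):

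| Blood share | Blood level only: r | Significant | Uptake only: r | Significant |
|---|---|---|---|---|
| 21% | 0.27 | 35% | 0.53 | 92% |
| 50% | 0.42 | 72% | 0.42 | 73% |
| 79% | 0.53 | 92% | 0.27 | 35% |
| 85% | 0.55 | 94% | 0.23 | 26% |

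In the blood-only columns the true correlation with uptake is zero, so the observed value is inflated. In the uptake-only columns the true 0.6 is attenuated. If both components matter in the same direction, inflation is again possible. For example, with equal shares and an assumed correlation of 0.4 with each, the observed value is 0.4 × 0.71 + 0.4 × 0.71 = 0.57.

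At a 50% share the two explanations give practically the same result. The MRS value alone cannot choose between them.

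**The case against.** Four points can be made for the plan.

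- **A fuller document may cover it.** The article refers to an imaging protocol that it does not describe. Scan-day procedures, MRS quantification and model covariates are commonly left to the full protocol or analysis plan. This stands for the covariate and for the unstated interval between supplement and scan, neither of which is a fault of the article. It does not dispose of the point: Table 3 is the article's schedule of events and positively places blood ketones away from the scans. If a scan-day reading exists, the table needs correcting.
- **Pairing is not ruled out.** The monitor checks are tied to intervention days with ±10-day windows, and nothing forbids a check on the scan day. This stands: pairing is not provided for, but it is not shown to be impossible.
- **Blood level may be part of the mechanism.** Section 3.2 gives high circulating ketones as an element of the intervention. A path from blood to brain ketones to stability may be exactly what the trial wants to see, and adjusting for blood level would remove it. This stands, and it is why adjustment should not be the only analysis.
- **It concerns a secondary outcome in an exploratory open-label pilot.** Also true, and it limits the weight of the point.

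A reader might go further and infer that Hypothesis 2 really correlates stability with blood level and not with uptake. The documents do not support that. The signal carries both, and it would reduce to blood level only if uptake did not vary between participants. Nor do the hypotheses describe the MRS value as a fixed trait of the participant, and nothing shows that the error must be attenuation.

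**Conclusion.** The concern holds in this form: on the published schedule the MRS outcome cannot be distinguished from the circulating ketone level at the scan. Either result for Hypothesis 2, and for the MRS part of Exploratory Hypothesis 3, is therefore open to two explanations. The schedule gap rests on the article's own text and needs no assumption.

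The size cannot be fixed. The range of about 21% to 85% for the blood share rests on the multiplicative model, independence of its two terms and the assumed CVs. The correlations also rest on the assumed 0.6. The direction of the error is open too. The primary fMRI comparison and the sample size of 34 are unaffected. The matter should be settled before scanning, because a scan-day blood value cannot be recovered afterwards.

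**What to change.** - Take a Keto-Mojo ß-HB finger-stick at each MRS session, and mark it in the two imaging columns of Table 3.
- Record the time since the last supplement at each scan. This is a data item only and changes no dosing.
- Report Hypothesis 2 twice: with the raw MRS signal, described as brain ketone level, and with the signal adjusted for the paired blood ß-HB. Keep the word 'uptake' for the adjusted result. Treat the MRS part of Exploratory Hypothesis 3 in the same way.
- If no paired reading is taken, rename the outcome 'brain ketone level at scan'.

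Cost: two extra finger-sticks per participant on a device the trial already uses (2 × 34 = 68 for the net sample, at most 2 × 50 = 100 for the gross sample), and one extra covariate in a small sample. No extra visit is needed. A single finger-stick is itself an imperfect reading, so adjustment will reduce the ambiguity and may not remove it.
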